## Abstract

**Background:**

Antisocial behaviour and adult criminality often have their origins in childhood and are best addressed early in the child’s life using evidence-based treatments such as the ‘Incredible Years Parent Programme’. However, families with additional risk factors who are at highest risk for poor outcomes do not always make sufficient change while attending such programmes. Additional support to address barriers and improve implementation of positive parenting strategies while these families attend the Incredible Years Programme may improve overall outcomes.

The study aims to evaluate the efficacy of adding a structured home visiting intervention (Home Parent Support) to improve outcomes in families most at risk of poor treatment response from the Incredible Years intervention. This study will inform the design of a larger prospective randomised controlled trial.

**Methods/design:**

A pilot single-blind, parallel, superiority, randomised controlled trial. Randomisation will be undertaken using a computer-generated sequence in a 1:1 ratio to the two treatments arranged in permuted blocks with stratification by age, sex, and ethnicity. One hundred and twenty six participants enrolled in the Incredible Years Parent Programme who meet the high-risk criteria will be randomly allocated to receive either Incredible Years Parent Programme and Home Parent Support, or the Incredible Years Parent Programme alone. The Home Parent Support is a 10-session structured home visiting intervention provided by a trained therapist, alongside the usual Incredible Years Parent Programme, to enhance the adoption of key parenting skills. The primary outcome is the change in child behaviour from baseline to post-intervention in parent reported Eyberg Child Behavior Inventory Problem Scale.

**Discussion:**

This is the first formal evaluation of adding Home Parent Support alongside Incredible Years Parent Programme for families with risk factors who typically have poorer treatment outcomes. We anticipate that the intervention will help vulnerable families stay engaged, strengthen the adoption of effective parenting strategies, and improve outcomes for both the children and families.

**Trial registration:**

Australian New Zealand Clinical Trials Registry ACTRN12612000878875.

## Background

Child conduct problems are prevalent affecting an estimated 5 to 10% of children in New Zealand [1,2]. They negatively impact on parental wellbeing and result in increased demands on health, education, and social services [1,3]. Longitudinal studies have established that conduct problems in childhood are precursors to a range of adverse outcomes in adulthood [4,5]. Without effective intervention, these problems have the potential to lead to long-term problems including substance abuse, mental health difficulties, violent behaviour, and poor physical health [6]. Conduct problems, aggressive behaviour, and poor emotional regulation in young children are important predictors of later antisocial and criminal behaviour in some adolescents, and the effectiveness of interventions diminishes with age [1,2,4,6,7]. Therefore, it is prudent to identify those young people at risk and provide an evidence-based intervention early in the life of the child before problematic behaviours have become entrenched and parent–child relationships have broken down.

Intervening early in the life of the child has proven long-term benefits for children with challenging behaviour [5,8], and better outcomes for the family and the community than treatment in adolescent years [8,9]. Heckman [10] has identified the wider benefits from early childhood intervention, including improved learning in schools, as well as reduced crime, teenage pregnancy, and welfare dependency. Early childhood intervention is also cost-effective [3,11]. For example, Scott and colleagues [3] estimate the cost of public services used by an individual with conduct disorder to be ten times greater than an individual with no problems. Church [1] found similar costs in New Zealand with successful intervention for a 5-year-old costing approximately $5,000 compared to $60,000 for an adolescent. Furthermore, Church found the success rate is 70% greater for younger children.

Although genetic factors have a role in the development of challenging behaviour, it is the environmental factors that are more readily addressed. Behavioural and social learning theories posit that children learn behaviour within the context of their environment. Children raised in a positive and nurturing environment are more likely to have pro-social friendship skills, an ability to regulate their emotional responses, and achieve appropriate educational standards. On the other hand, children raised in environments with limited resources, by parents who have health problems, and who use punitive parenting practices are less likely to achieve good outcomes [2]. Intervening with an effective parenting programme has been shown to address many of the environmental factors contributing to the development of anti-social and aggressive behaviours in children, and improve their long-term outcomes [5,8].

The Incredible Years Parent Programme (IYP) is one evidence-based intervention with extensive research showing effectiveness for children with conduct problems [3,5,8,12,13]. Results have been replicated in a number of countries, e.g., Wales, Ireland, Norway, USA, Canada, England [14-17], and also for foster families where the children have additional high needs [18,19]. There is a small but growing body of literature demonstrating the effectiveness of IYP programmes in New Zealand, for example with Maori participants [9,20-22], single parents with children with Attention Deficit Hyperactivity Disorder [23], and within the Ministry of Education [22,24,25]. However, despite these good results, a third of children with behavioural problems whose parents attend IYP still experience difficulties and are at risk of developing chronic problems in adolescence [17,26]. In a trial with children initially within the clinical range, Webster-Stratton et al. [5] found that post-treatment child behaviour scores remaining within the clinical range was a predictor of adolescent engagement in delinquent acts; achieving post-treatment scores within the normal range was more likely to result in better long-term outcomes.

Those who do poorly despite treatment often have risk factors that are identifiable prior to intervention. While the literature is varied on which specific factors attribute to poor treatment outcomes, the factors generally cluster into four categories [7,15,27-30]:

i. Child variables (severity of child behaviour, referral source, sex).

ii. Parent variables (maternal psychopathology/depression, coercive/punitive parenting style, maternal age, negative life events/stressors).

iii. Family demographics (single parent, family size, low income, education/occupation, maternal age, minority status).

iv. Participation variables (treatment attendance, perceived barriers to treatment participation).

Other factors for poor response to treatment identified in the literature [12,15,28,31] and those observed from personal experience of delivering the programme (Unpublished) include lack of partner support, resistance to change in the home, parents’ unrealistic and developmentally inappropriate expectations for children, adverse child rearing practices, and negative cognitions and perceptions of child behaviour. Reyno and McGrath [29] concluded from their meta-analysis that providing additional support to parents attending parent training may improve outcomes for high risk families.

In recognition of the need to provide additional support for families attending the IYP programme, the New Zealand Ministries of Health and Education established the Incredible Years Specialist Service (IYSS) as a collaborative venture. This service provides a targeted intervention, Home Parent Support (HPS), for families of young children who are identified as greater risk of non-response to treatment for conduct problem behaviours. The specification for IYSS is to provide a comprehensive inter-agency intervention to address conduct/antisocial behaviour and associated mental health problems in children. Key features include:

• Strengthening and supporting a coordinated interagency response;

• Bringing mental health expertise and capacity to a multi-agency team;

• Strengthening interventions for Maori families;

• A focus on children aged 3–7 years; and

• Prioritising those with more severe conduct problems.

The joint commitment from the Health and Education sectors to work collaboratively should improve access to parent information, child health, and educational services for vulnerable families at an optimum time in the life of the child. It is expected that this support will improve engagement in IYP and improve overall outcomes. However, we do not have robust evidence that HPS does improve outcomes compared with IYP alone. The aim of this study is to evaluate the effectiveness of adding a structured home intervention while the parent/carer attends IYP.

As in all group parent programmes, most home visiting programmes are based on the premise that parents play an important role in shaping the outcomes of their children, and that intervention in early childhood ensures input in a sensitive developmental period [27,32]. There is also an increasing awareness of the importance of the early caregiving environment and the impact this has on early neurological development [33]. Over the last 20 years, there has been an increase in home visiting programmes in an attempt to address child maltreatment, reduce infant mortality, and improve child wellbeing [34]. Home visiting allows interventions to be tailored to the specific needs of the family and provides therapists with the opportunity to assess and address other risk factors such as substance abuse, poor parental mental health, and violence in the home [35].

In spite of the growing popularity of home visiting programmes, reviews report mixed results [33,35]. There are only a few programmes that have demonstrated long-term benefits for parents and children [36-38]. The diverse results of home visiting programmes, in general, give some indication of how difficult it is to change parenting practices once dysfunctional patterns have become the established norm for the family [34]. Gomby [35] suggests that combining an effective home visiting programme with other education programmes may improve outcomes.

Characteristics that contribute to an effective home visiting programme include internal consistency (adherence to the curriculum), a collaborative approach when working with parents, well trained and well supervised therapists, close relationship with other services, and low caseloads [33,35]. These factors are key components of the HPS intervention developed by DL to support families to maximise the benefits of IYP.

HPS provides a structured intervention for parents in their home in conjunction with attending IYP. Parents have the benefit of the IYP group curriculum on child development and parenting practices, experiential group learning, and socialisation. HPS is provided by therapists who are trained mental health workers and accredited IYP facilitators. They are familiar with the detail of the course content and key principles, and work collaboratively with the parents in their home. They support parents to implement the key parenting principles and practice new skills, and tailor these strategies to their own circumstances. Therapists focus on building the parent–child relationship and on addressing negative cognitions and coercive patterns of interaction. They also assess barriers for change and support parents to access other appropriate health and education services such as adult mental health services, income support, relationship services, and special education services. Therapists follow a structured guide to ensure adherence to the curriculum and they attend weekly supervision to maintain fidelity. In an open trial of HPS participants reported high levels of satisfaction and retention rate was high at 92% (Unpublished).

We hypothesise that the addition of a structured home intervention (HPS) will result in better outcomes for families with additional risk factors for poor treatment response, and we expect to increase the percentage of children with post-treatment scores in the non-clinical range. The current study has been designed to evaluate this intervention and, if it is found to be effective, there is the potential for national implementation.

The successful widespread implementation of any intervention requires a degree of pragmatism. To identify families at greater risk of non-response it would be unrealistic to try and screen for all the factors outlined above, and a number of them cluster together. Three domains have been used in this study to identify families at greater risk of non-response. These are from the categories of the overall risk factors and would be easy to implement in a community real-world setting.

1. Child behaviour scores in the clinical range on standard child behaviour psychometrics and/or school exclusion.

2. Poor parental mental health.

3. Involvement of Child Youth and Family Social Services indicting abuse or neglect (as a proxy measure of coercive parenting).

## Methods/design

### Design

This study is a pilot single-blind, parallel, superiority, randomised controlled trial. Eligible participants will be randomly allocated to receive IYP plus HPS or to the control group of IYP treatment alone. Randomisation will be undertaken using a computer-generated sequence in a 1:1 ratio to the two treatments arranged in permuted blocks. Stratification will be by age, sex, and ethnicity. Data from all participants will be included in the data analysis, irrespective of whether follow-up data is available using an intention-to-treat design.

### Ethical approval

Approval has been received from the New Zealand Northern B Health and Disability Ethics Committee (NTY/12/06/050).

### Setting

This study is being carried out in a real-world setting within the Bay of Plenty District Health Board, Tauranga, New Zealand.

### Participants

Participants are parents/caregivers of children with conduct problems recruited from IYP groups delivered in the community by the Child and Adolescent Mental Health Services (CAMHS), the Ministry of Education, and non-government organisations in Tauranga. Parents attending IYP are either self-referred or referred by health or education services. Criteria for parents to attend IYP are: they speak English, have the child in their custody or have regular access arrangements, and their child does not have an intellectual disability. All families attending IYP are screened for eligibility for IYSS and those who meet the criteria will be invited to take part in the trial until 126 participants have been recruited. Participants will be randomly allocated to IYP plus HPS or to IYP alone. Where there is more than one child in a family who meets the criteria for IYSS, the parent will identify the child they find most challenging as the focus child. Where more than one parent/carer is attending IYP, and their child meets the criteria for IYSS, one parent/carer will be identified as the trial participant.

### Inclusion criteria

Participants will be eligible for inclusion in the trial if:

• They are parents/caregivers of children with conduct problems, who are enrolled to attend IYP.

• Their child is over 3 years and under 8 years of age on the date of signed consent to participate in the trial.

• Parent child behaviour scores are in the clinical range for any of the following psychometrics: Eyberg Child Behavior Inventory (ECBI) total problem scale >11; ECBI intensity scale >127; Social Competency Scale (SCS) <17.

• Or there is one of the following risk factors: Child, Youth and Family Services involvement; school exclusion; parent diagnosed with mental health disorder.

### Exclusion criteria

None.

### Withdrawal criteria

Participants can withdraw from the intervention at any time but will remain in the trial. If participants require on-going support they will be assisted to engage in an appropriate community agency.

### Intervention

#### HPS

Participants will receive 10 in-home sessions from a separate therapist accredited in IYP whilst they attend the 14 to 16 week Basic IYP. The intervention will include a comprehensive child assessment, including developmental, medical, and social history, pre-school or school reports, involvement of other agencies, family structure, and parental mental health. Participants will be supported to identify specific goals they wish to achieve and record them. The therapist will visit them in their homes to provide support to personalise and implement the IYP strategies and to address any barriers to implementation of these strategies that they or the therapist identifies. The therapist will follow a structured intervention guide to ensure therapist fidelity. Treatment includes follow-up contact at one-month post-intervention to assess stability of change and provide further assistance if required.

The therapists delivering HPS will meet weekly to review all participants’ progress and identify any additional support required for families. Therapists will have fortnightly contact with IYP group leaders to review attendance and participant progress. Participants will be reviewed monthly by a multidisciplinary team that includes a Child and Adolescent Psychiatrist, Paediatrician, Ministry of Education IYP co-ordinator, and the HPS therapists. Specialist psychiatric and/or paediatric assessment is available if required. This multidisciplinary team will also review any adverse events and assess the likelihood that this may be related to the intervention.

#### Therapist guide

The therapist guide specifies the important components of the home intervention. It identifies key elements for each session to ensure the intervention is focussed on the content and learning from IYP and that the learning occurs in a supportive collaborative manner to encourage and motivate participants. The key elements of HPS include reviewing IYP principles, tailoring strategies, practicing and rehearsing new skills, therapist modelling praise and affirmation, identifying and reviewing participant goals, and addressing barriers to implementation of new skills.

#### Intervention fidelity

HPS therapists will follow the structured guide in their intervention and keep a record of activities in each session to ensure that key activities are included. This record will be reviewed in weekly supervision.

### Control

Participants will be in the same IYP groups as those in the intervention arm. This is to prevent real or perceived difference between the groups. All IYP groups will be delivered by trained facilitators in CAMHS, the Ministry of Education, or non-government organisations and will receive 2 hours supervision fortnightly. Those in the control will receive the usual support from IYP group leaders and will still have access to all services that would normally be available to them.

### Outcomes

#### Primary outcome

The primary outcome is a change in child behaviour from baseline to post-intervention in the parent-reported ECBI Problem scale.

#### Secondary outcomes

• The percentage of parent scores on the ECBI that are in the normal range at post-treatment.

• The percentage of parent scores on the Child SCS that are in the normal range at post-treatment.

• Changes from pre- to post-intervention in child behaviour, parenting practices, parent relationships, and parental well-being measured on the Family Questionnaire (FQ) scales.

• The percentage with at least 80% engagement in IYP measured on the attendance register.

• Levels of parent satisfaction with IYP measured using the Parent Satisfaction Questionnaire.

• Maintenance of improvement at 6-month follow-up measured on the FQ, ECBI, and SCS.

• Parent reports of competence with implementing IYP strategies in the home as reported in the Follow-up Questionnaire at 6 months.

#### Baseline

Once eligibility is confirmed a research assistant will collect pre-intervention baseline data on demographics and the FQ. The FQ was developed by the Incredible Years Pilot Study Working Group for use in a joint-agency national evaluation of Incredible Years Pilot Study [43]. The questionnaire is a comprehensive assessment of child behaviour, parenting practices, partner relationships, parental depression, life events, cultural participation, and parent satisfaction. The research assistant will read all questions out to the participant and score responses on the questionnaire.

#### Post-treatment

The IYP group leaders will collect post-treatment measurements using the ECBI, SCS, and the standard Incredible Years Parent Satisfaction Questionnaire. This is a 24-question assessment of parent views on the programme content and teaching methods. Parents rate their satisfaction on 1- to 7-point Likert scale [44]. The research assistant will repeat the relevant sections of the FQ within two weeks of the final IYP session.

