#### Follow-up

At the 6-month follow-up, the research assistant will collect ECBI, SCS, and FQ and a quantitative/qualitative follow-up questionnaire. This questionnaire includes Likert-type scales and opportunities for written feedback to assess levels of engagement, helpful aspects of the trial, level of competency with implementing IYP strategies, and changes in relationships and behaviour noticed by parent/carers (Table 1).

**Table 1 T1:** Summary schedule of data collected

**Method of data collection**	**Screening**	**Baseline**	**Post-intervention**	**6-month follow-up**
ECBI & SCS*	**X**		**X**	**X**
Demographics		**X**		
FQ		**X**	**X**	**X**
PSQ			**X**	
Follow-up Questionnaire				**X**

ECBI, Eyberg Child Behavior Inventory; FQ, Family Questionnaire; PSQ, Parent Satisfaction Questionnaire; SCS, Social Competency Scale. *Screening is within 3 weeks of baseline data collection.

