### Blinding

Due to the nature of the study, it is not possible to have a completely blinded design. Participants will know which intervention they are receiving. IYP group leaders will also know who is in the treatment arm as their contribution is a part of the HPS intervention. The primary investigator leads the IYSS team and conducts the multidisciplinary team review and will therefore be aware of those participants in the treatment arm. However, the research assistant undertaking the assessments will be blind and remain blind to treatment allocation throughout the study. Participants will be asked not to reveal the intervention they are receiving to the research assistant. All participants will be given an identification number to ensure the researcher and all those involved in summarising and inputting the data are unaware of the treatment allocation.

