### Qualitative analysis

A small number of qualitative questions are included in the questionnaires to assess participants’ unique perspective and experience of the intervention. At baseline, open questions include reasons for referral to IYP and asking parents about their expectation of the intervention. Post-treatment questions explore the parents experience of the intervention they received (HPS or IYP alone) and what, if any, benefits they have gained. Follow-up questions focus on changes in child behaviour and parent–child relationships. Questions also focus on the parents’ experience of being part of the trial and any suggested improvements.

Responses will be coded using a general inductive approach described by Thomas [46]. All responses will be read systematically to identify meaningful units. These will be coded and then categorised into emerging themes. Any links or relationships between the themes will be established. The frequent, dominant, or significant themes will be identified, and will inform research findings. Participants’ responses to open ended questions are expected to give insight into the impact of child behaviour on the family, their expectations and hope for change, and their experience of the intervention, including unplanned or unanticipated effects. An independent coder will code 30% of transcripts to ensure reliability of coding. Any discrepancy in themes will be resolved by agreement between the two coders (Additional file 1).

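### The post-treatment ECBI, which determines the primary outcome, is collected by unblinded IYP group leaders, so the stated assessor blinding does not cover the primary endpoint

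*Protocol article*

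**What the plan says.** All references are to the protocol article.

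- **Primary outcome:** "The primary outcome is a change in child behaviour from baseline to post-intervention in the parent-reported ECBI Problem scale".
- **Post-treatment:** "The IYP group leaders will collect post-treatment measurements using the ECBI, SCS, and the standard Incredible Years Parent Satisfaction Questionnaire". The research assistant's task at this point is to repeat parts of the FQ, no later than two weeks after the last IYP session.
- **Blinding:** "IYP group leaders will also know who is in the treatment arm as their contribution is a part of the HPS intervention". The HPS section describes their link with the HPS therapists: "Therapists will have fortnightly contact with IYP group leaders to review attendance and participant progress".
- **Blinding**, on the assessor: "the research assistant undertaking the assessments will be blind and remain blind to treatment allocation throughout the study". The Abstract and the Design section call the trial single-blind.
- **Follow-up:** "At the 6-month follow-up, the research assistant will collect ECBI, SCS, and FQ and a quantitative/qualitative follow-up questionnaire".
- **Statistical methods:** missing data are handled first by last observation carried forward, with multiple imputation as a sensitivity analysis. The same section promises considerable effort to obtain data from parents who do not complete treatment.

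**The concern.** The Blinding section reads as though a blind research assistant carries out the outcome assessments. For the primary endpoint that is not so. The people who collect the decisive ECBI know the allocation and have a part in the experimental arm only.

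The ECBI is a parent report, so what is at stake is the collector's influence on it. A group leader may prompt. A parent may wish to please the leader they have met for 14 to 16 weeks. Forms may be chased harder in one arm than in the other.

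Collection through group leaders is also easiest from parents who still attend, and attendance is something HPS is meant to improve. A missing score is then replaced by the earlier one, so uneven collection feeds directly into the primary comparison.

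The trial is a pilot meant to inform the power calculation of a larger trial and possibly national policy. An effect inflated in this way would be carried forward into both.

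**Working it through.** **1. Who collects the ECBI, and when** (Screening measurement, Baseline, Post-treatment, Follow-up, Table 1, Blinding)

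| Time | ECBI collected by | Collector knows allocation? | Research assistant collects |
|---|---|---|---|
| Screening | Group leaders | No; randomisation comes later | Nothing stated |
| Baseline | Not collected | – | Demographics, FQ |
| Post-treatment | Group leaders | Yes | FQ sections |
| 6 months | Research assistant | No | ECBI, SCS, FQ, follow-up questionnaire |

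The primary outcome uses the screening and post-treatment rows. The blind research assistant collects the ECBI in neither. Exposure to an unblinded collector is confined to the post-treatment row, because no allocation exists at screening.

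**2. The plan's own power figure** (Sample size; context only)

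- Standard error of a standardised difference with 50 per arm: √(2/50) = 0.20.
- Power at d = 0.57, two-sided α = 0.05: Φ(0.57/0.20 − 1.96) = Φ(0.89) ≈ 81.3%. The t-test gives 80.6%. The stated 80% is reproduced.
- Allowing for 20% loss: 100/0.80 = 125, against the stated 126.

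Changing the collector alters neither the sample size nor the power.

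**3. How missing scores enter**

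Table 1 shows no ECBI at baseline, so the value carried forward to post-treatment is the screening score and the change becomes zero. Suppose both arms truly improve by the same mean Δ, parents with missing scores included. Let m_C and m_H be the proportions missing in the control and HPS arms. The expected difference between arms is then

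(1 − m_H)Δ − (1 − m_C)Δ = (m_C − m_H)Δ.

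This favours HPS if more control scores are missing, and the control arm if more HPS scores are missing. The Sample size section gives 80% completion for parents receiving HPS and no control figure, so neither sign nor size can be settled.

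**4. What an arm-differential collector effect could do** (assumption, not from the document)

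Let the collector shift the difference between arms by b SD when the true effect is zero. The two-sided rejection rate is

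1 − Φ(1.96 − b/SE) + Φ(−1.96 − b/SE), with SE = √(2/n).

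| b (SD) | n = 50 per arm | n = 63 per arm |
|---|---|---|
| 0 | 5% | 5% |
| 0.1 | 8% | 9% |
| 0.2 | 17% | 20% |
| 0.3 | 32% | 39% |

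For example, b = 0.2 with n = 50 gives b/SE = 1.0, so 1 − Φ(0.96) + Φ(−2.96) ≈ 0.17. The table shows how sensitive a trial of this size is. It is no estimate of b.

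**The case against.** The strongest counter-argument is that the collector is not the rater. The parent supplies every ECBI answer and knows the allocation, so no choice of collector makes the primary outcome blind. The protocol says that leaders collect the form. It does not say that they read it aloud or score it, so their room for influence is unknown. The Blinding section also discloses openly that leaders are unblinded. All of this stands. It limits the gain from a blind collector to removing collector influence, and it makes bias towards HPS a risk rather than an established fact. It does not remove the mismatch between the Blinding and Post-treatment sections.

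A reader might infer more than the document supports:

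- **That both ECBI measurements are compromised.** The screening value precedes randomisation.
- **That about 25 families (126 × 0.20) will be missed.** The 80% refers to completion of IYP among parents receiving HPS, not to data collection. The protocol promises efforts to reach non-completers and does not limit ECBI collection to attenders. What remains is that this task falls to the staff least likely still to be seeing those parents.
- **That the switch to the research assistant at 6 months confounds the maintenance analysis.** The switch happens in both arms, so a uniform effect cancels. Only an arm-differential effect survives, which is the same concern again.
- **That the post-treatment qualitative questions unblind the assistant.** The Qualitative analysis section asks about the intervention received but does not say which questionnaire holds these questions or who administers it.
- **That the bias is some share of the effect the trial was sized for.** The Sample size section says there was no formal power calculation; 0.57 is the effect detectable with 50 per arm.

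**Conclusion.** The point holds in limited form. The blinding that supports the single-blind label does not reach the primary endpoint: the post-treatment ECBI is collected by people who know the allocation and contribute to HPS, while the blind assistant collects only a secondary measure at that time. This follows from the document's own statements and needs no assumption.

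The size of any resulting bias cannot be computed from the document. The rejection rates above depend wholly on an assumed shift, and the effect of carrying scores forward depends on missing-data rates by arm that are not given. A blind collector would remove avoidable collector influence and loosen the tie between collection and attendance. It would leave the bias of an unblinded respondent in place.

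The change is worth making because the blind assistant is already due to contact the same parents at the same assessment point.

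**What to change.** 1. Have the blind research assistant collect the post-treatment ECBI and SCS at the FQ contact already scheduled after the last IYP session, for every randomised parent whether or not they completed IYP. Group leaders keep the satisfaction questionnaire.
2. Reconcile the Post-treatment and Blinding sections so that both name the same collector.
3. For families already assessed by group leaders, record who collected each ECBI and report a sensitivity analysis of the primary outcome by collector. Randomisation is stratified by IYP group, so switching a whole group at a time would keep the collector balanced between arms.
4. If the collector is not changed, state plainly that the primary outcome is not collected blind and that the single-blind description applies to the research assistant's measures.

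**Cost:** 36 + 12 = 48 items added to a contact already planned, hence slightly longer interviews, with a short amendment to the text. No new visit is needed, and the assistant already collects both scales at 6 months. The main drawback is a change of collector partway through, since the Trial status section says recruitment began in March 2013; step 3 addresses this.
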